## Abstract

**Background:**

The surgical technique used in liver transplantation has undergone constant evolution in an effort to develop a safe, highly standardized procedure. Despite this, the initial step of recipient hepatectomy has not been the focus of clinical research thus far. Due to advanced coagulopathy in liver transplant recipients, this part of the operation still carries the risk of severe hemorrhage. This trial is designed to compare an electrothermal bipolar vessel sealing device (LigaSure™) and an ultrasound dissector (HARMONIC ACE®+7) with standard surgical techniques during the recipients’ hepatectomy in liver transplantation.

**Methods/design:**

In a single-center, prospective, randomized, controlled, parallel, three-armed, confirmatory, open trial, LigaSure™ and HARMONIC ACE®+7 will be compared with standard surgical techniques that use titanium clips and conventional knot-tying ligations during recipient hepatectomy in liver transplantation. Intraoperative total blood loss is the primary endpoint of the trial. Secondary endpoints include blood loss during hepatectomy, the duration of both the hepatectomy and the entire surgical procedure, and blood transfusion requirements of the procedure. To generate reliable data, intraoperative blood loss will be recorded with respect to all rinse fluids during surgery, ascites, and by weighing used swabs. At 80% power and an alpha of 0.025 for both of the experimental groups, 23 subjects will be analyzed per protocol in each study arm in order to detect clinically relevant reduction of intraoperative blood loss. The intention-to-treat analysis will include 69 patients. The follow-up period for each patient will be 90 days for safety reasons, whereas all clinical outcomes will be measured within the first 10 postoperative days.

**Discussion:**

To our knowledge, this is the first prospective, randomized trial comparing two innovative technical methods of vessel sealing and dissection with standard techniques for recipient hepatectomy. This will be done to detect relevant reduction of intraoperative blood loss during liver transplant. The results of the trial are expected to improve patient outcome and safety after liver transplant and to increase the general safety of this procedure.

**Trial registration:**

ClinicalTrials.gov, NCT 03323242. Registered on October 26, 2017.

**Electronic supplementary material:**

The online version of this article (10.1186/s13063-018-2778-1) contains supplementary material, which is available to authorized users.

## Background

Liver transplant (LT) is a well-established procedure for the treatment of end-stage liver disease. Many improvements in the surgical technique have rendered this operation relatively safe. Most important operative innovations after the initial introduction of LT in the clinical routine undertaken by Starzl include the use of venovenous bypass in LT [1, 2]; the piggyback technique with preservation of the recipients’ caval vein [3]; and its modification, which was introduced by Belghiti with side-to-side cavocaval anastomosis [4]. Nevertheless, very few improvements have been introduced in the surgical technique with regard to tissue preparation and sealing the blood vessels during recipient hepatectomy. Due to end-stage liver disease and the recipients’ general and coagulatory condition, hepatectomy carries the risk of severe blood loss (BL), which can impair the outcome after LT. Usually, recipient hepatectomy is carried out as a combination of sharp dissection of the hepatic adhesions to the abdominal wall and the diaphragm and clip or suture ligature of small retrohepatic caval vein branches [5].

With advances in surgical procedures and equipment, modern technologies have been introduced that have shortened operation time and improved surgical outcomes. Exquisite equipment for liver parenchymal transection, such as Cavitron ultrasonic surgical aspirator (Integra LifeSciences, Plainsboro NJ, USA), ultrasonic dissector (USD), LigaSure™ (LS; Covidien, Medtronic, Minneapolis, MN, USA), and TissueLink (Medtronic, Minneapolis, MN, USA), can also be used to reduce hemorrhage in liver resection [6]. The ultrasonic scalpel (Ethicon, Bridgewater, NJ, USA) is a USD that cuts and coagulates tissue using ultrasound at frequencies higher than those used with an ultrasonic aspirator [7]. This device can also serve as a grasper and basically uses a blade that oscillates at 55 kHz, thus producing heat and enabling coagulation of vessels. Recently, its use and potential advantages in open liver resection have been demonstrated. The main technical advancement in this field relates to decreased intraoperative bleeding [8, 9]. Olmez et al. [10] described dissection of the small retrohepatic veins with a USD (HARMONIC™ scalpel; Ethicon) during recipient hepatectomy. Their results showed that this method is safe when compared with conventional knot-tying ligation regarding intra- and postoperative bleeding rate.

The LS electrothermal bipolar vessel-sealing device is another alternative; it applies electrothermal bipolar coagulation and dissection in one step. The LS dissection device seals the tissue first, before it is divided; both tasks are performed with the same device. This may prevent severe bleeding. Furthermore, the sealing device is capable of coping with small liver veins that can be sealed and divided safely without the need for sutures or clips, the latter of which are known for interfering with sufficient “tangential” clamping of the inferior vena cava (IVC) for side-to-side cavocavostomy during piggyback LT [11]. In 2012, Lamattina et al. [12] reported the use of LS devices for recipient hepatectomy in LT. They concluded that LS vessel sealing was an efficient method and that vessel sealing of the caval and portal veins as well as other structures could be safely performed in the setting of end-stage liver disease.

To our knowledge, no randomized clinical trial has been conducted to compare various innovative dissection methods against the standard techniques used for recipient hepatectomy. While LS and USD have been proven to be used safely in several major surgical procedures, including liver resection [13–20], their ability to reduce BL in LT recipient hepatectomy has not yet been evaluated systematically.

## Methods/design

This is a single-center, prospective, randomized, controlled, parallel, three-armed, confirmatory, open trial. This trial is designed to evaluate the potential beneficial effects (superiority design) of using an LS device and USD for recipient hepatectomy during LT. Furthermore, the practicability of these methods is to be investigated. Both the duration of the procedure and the BL during both the entire surgery and the hepatectomy phase of transplant are of interest.

### Hypotheses

Null hypotheses:

• The intraoperative BL does not differ in any clinically relevant extent between the control group and USD with (H0_1_): BL 1 = BL 2.

• The intraoperative BL does not differ in any clinically relevant extent between the control group and LS with (H0_2_): BL 1 = BL 3.

Alternative hypotheses:

• The intraoperative BL differs in a clinically relevant extent between the control group and USD with (H1_1_): BL 1 ≠ BL 2.

• The intraoperative BL differs in a clinically relevant extent between the control group and LS with (H1_2_): BL 1 ≠ BL 3.

### Setting

This investigator-initiated trial is set at a single referral center which is specialized in visceral transplant surgery. All LTs are carried out within a structured, interdisciplinary LT program that has been externally reviewed and accredited.

### Outcome measures

#### Primary endpoint

Total BL during surgical procedure

#### Secondary endpoints

BL during recipient hepatectomyTime from skin incision to end of hemostasis after hepatectomyTime from skin incision to end of skin closureHemodynamic status during surgery: Data on the mean arterial pressure and central venous pressure (CVP) will be obtained at the beginning of hepatectomy after incision and adhesiolysis.Coagulation state: International normalized ratio (INR), partial thromboplastin time (PTT), and platelet counts of patients will be recorded pre- and postoperatively until postoperative day (POD) 10.Hemoglobin (Hb) level: Hb levels of patients will be recorded pre- and postoperatively until POD 10.The number of units of packed red blood cells (PRBC) transfused during surgeryThe number of fresh frozen plasma (FFP) units transfused during surgeryThe number of platelet units transfused during surgeryPostoperative PRBC and FFP transfusion until POD 10Postoperative bleeding: Postoperative hemorrhaging until POD 10 will be recorded and classified as defined by Dindo et al. [21].Postoperative morbidity: Postoperative morbidity will be recorded and classified as defined by Dindo et al. [21].Retransplant rateConversion rate to alternative methods during recipient hepatectomy in LS and USD groups

### Procedures and methods

#### General description

After incision through the abdominal wall, depending on the randomization result, the electrothermal bipolar vessel sealing device (“LS”, LigaSure™ Maryland Jaw 23 cm Open Instrument; Covidien plc), an ultrasound dissector (“USD”, HARMONIC ACE®+7 Shears; Ethicon), or standard methods applying titanium clips and ligations will be used for mobilization of the liver from its adhesions and ligaments as well as for dissection and coagulation of retrohepatic IVC branches and other small blood vessel-bearing structures. Tissue coagulation and dissection will be carried out in small portions according to the manufacturer’s instructions. The dissection of the small blood vessels and the connective tissue in the hepatoduodenal ligament will also be carried out with LS or USD in the experimental groups, whereas the common bile duct, hepatic artery, and portal vein, as well as the major hepatic veins (left, middle, and right), will be divided with endovascular staplers or conventional knot-tying ligations.

#### Therapeutic effects

Previous studies have reported that both LS and USD devices can be used safely for recipient hepatectomy in LT [10–12]. High-volume LT centers have reported intraoperative BL with average values between 1000 and 2100 ml [22–24]. In our experience, BL during LT could be reduced to about 835 (± 560) ml using LS for recipient hepatectomy [11].

##### Undesirable effects/risks

Participation in the trial will not cause additional invasive treatment (e.g., venous puncture for blood sampling) for the subjects. Like any other surgical procedure, freeing the liver from its adhesions and ligaments and dissecting the retrohepatic IVC branches bears the risk of bleeding and impairs other anatomical structures in the operating field. Nevertheless, preparation and dissection using LS and USD have been proven to reliably control bleeding in daily use during a variety of surgical procedures. A systematic review of randomized controlled trials in which LS was compared with other vessel-sealing devices did not reveal any safety concerns associated with the method [25]. Because LS and USD will be applied according to their designated indication within the approved parameters, no unreasonably hazardous risks are expected.

#### Blinding

Blinding the surgical staff is impossible due to the use of different methods in the three groups under investigation. Because the primary endpoint “total BL” will be precisely recorded during surgery by independent staff and secondary endpoints are objective physiological findings, blinding of the subjects is not needed. Therefore, the open design is not expected to cause any avoidable bias.

#### Randomization protocol

Sixty-nine LT recipients are expected to be randomized into three groups of at least 23 patients each:LS groupUSD groupControl group, using conventional bipolar coagulation devices, surgical suture ligatures, and surgical clips (or any dissecting/coagulating device other than LS)

Randomization will be performed using the “block randomization” method. Each block will contain multiple balanced combinations of the three groups: LS, USD, and control. Blocks will be randomly chosen (using simple randomization software with Excel® [Microsoft, Redmond, WA, USA]), and assignment of the participants to the respective groups will be determined. Randomization will be performed at any time between the inclusion of the patients according to the above-listed inclusion criteria and the beginning of recipient hepatectomy. Randomization will be performed by a member the clinical trial center (Klinisches Studien Zentrum [KSC]) of the surgical department of the University Hospital Heidelberg who is not otherwise involved in the trial. Afterward, the staff will personally inform the responsible surgeon about the treatment group to which the patient has been randomized.

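### The control group is defined so that it literally admits the ultrasonic dissector, one of the two devices under test, and this conflicts with the narrower control described elsewhere

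*Protocol article*

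**What the plan says.** The protocol article describes the control group in three places.

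- **Abstract, Methods/design:** the two devices are compared with "standard surgical techniques that use titanium clips and conventional knot-tying ligations".
- **Procedures and methods, General description:** depending on the randomization result, LS, USD or "standard methods applying titanium clips and ligations" are used to mobilize the liver. Device dissection in the hepatoduodenal ligament is assigned to the experimental groups.
- **Randomization protocol:** the list of the three groups gives control as conventional bipolar coagulation devices, suture ligatures and clips, "or any dissecting/coagulating device other than LS".

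The Background says that the ultrasonic scalpel "is a USD that cuts and coagulates tissue using ultrasound". The first null hypothesis (H0_1) is that blood loss "does not differ in any clinically relevant extent between the control group and USD". The second (H0_2) makes the same statement for control and LS.

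On departures from the assigned method, the secondary endpoint list gives a conversion rate for the LS and USD groups only. The data list for the day of surgery collects conversions in all three groups, together with protocol violations. Course of the study says that protocol deviations are recorded.

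**The concern.** The USD dissects and coagulates, and it is not LS. It therefore falls within the control definition in the Randomization protocol section, although it is the treatment in one of the two arms that control is meant to be compared with. No section expressly bars it from control patients.

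Both confirmatory contrasts use the same control group. If some controls are operated on with the USD, the control-versus-USD difference shrinks towards zero, and the comparator for LS becomes a mixture of standard technique and a device under test. The trial is open and the surgeon is told the allocation, so the written definition is the main thing that keeps the arms apart. If use of the USD in a control patient can be read as assigned treatment, a per-protocol analysis has no clear ground for setting that patient aside.

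**Working it through.** **1. The definitions side by side**

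| Place | Control technique | LS in controls | USD in controls |
|---|---|---|---|
| Abstract | clips, knot-tying ligations | not part of it | not part of it |
| General description | clips, ligations | not part of it | not part of it |
| Randomization protocol | bipolar coagulation, suture ligatures, clips, or another device | excluded by name | admitted by the wording |

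Bipolar coagulation also appears only in the third row, so the mismatch is wider than the USD alone.

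**2. How USD use in a control patient would be classified**

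- Against the Randomization protocol section, it fits the assigned arm.
- Against the abstract and the General description, it departs from the assigned arm.
- The day-of-surgery data list has a place to record a control-group conversion, but the endpoint list does not analyse one.

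The article gives no order of precedence between these sections, so the classification is open.

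**3. The plan's own sample-size figure**

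Inputs from Sample size estimation: means 1500 and 1035 ml (difference 465 ml), SD 560 ml, two-sided alpha 0.025, power 80%, superiority margin 50 ml, 23 per arm.

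The figure of 23 does not reproduce from these inputs. With the noncentral t, 29 per arm are needed if the margin is ignored and 36 if it is subtracted (normal approximation: 28 and 35). At 23 per arm, power is 69% and 58% respectively. That is a separate matter. It is stated here because it sets the starting point of the illustration.

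**4. Illustration of dilution**

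Let p be the share of controls given the USD. The documents give no value for p, so it is an assumption. Suppose these patients then have the USD mean and the SD stays at 560 ml.

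- Expected difference: d(p) = 465 × (1 − p). Each 10% of controls removes 46.5 ml.
- Standard error: 560 × √(2/23) = 165.1 ml.
- Noncentrality: d(p)/165.1, or (d(p) − 50)/165.1 with the margin subtracted. There are 44 degrees of freedom, and the critical value is 2.321.

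| p | d(p), ml | Power, margin ignored | Power, margin subtracted |
|---|---|---|---|
| 0% | 465 | 69% | 58% |
| 10% | 418.5 | 59% | 47% |
| 20% | 372 | 48% | 36% |
| 30% | 325.5 | 37% | 27% |
| 50% | 232.5 | 19% | 12% |

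A mixed control group also has a larger variance, 560² + p(1 − p) × 465². Allowing for this with the margin ignored gives 57%, 46%, 35% and 18% for p = 10%, 20%, 30% and 50%, a small further loss.

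**The case against.** The strongest reply is that the article as a whole shows what is meant. The General description sets out three alternatives that follow the randomization result and places device dissection in the experimental groups. The abstract agrees with it, and USD is listed as a group of its own. On this view the parenthesis is a slip of wording, and nothing else suggests that the authors chose to allow the USD in controls. The day-of-surgery list also collects control-group conversions, which implies that some methods lie outside the control technique.

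Much of this stands, and it rules out two stronger readings. A reader might infer that a control operated on with the USD would be fully compliant with the protocol. The documents do not support that: such a case fits the Randomization protocol section but conflicts with the abstract and the General description. A reader might also infer that such use would go unrecorded and would stay in the per-protocol analysis. That is not shown either, since deviations and control-group conversions are recorded and the article does not define the per-protocol set. What can be said is that the classification is unclear.

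The reply does not remove the conflict. The narrower descriptions do not say that other devices are barred, and the section that lists the randomized groups says that all but one are allowed. This is not a detail left to a fuller document: the article states the definition, and it does not suit a trial in which USD is an experimental arm.

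It is also fair to object that the power figures are hypothetical. The share p is unknown, and p = 0 is compatible with the abstract and the General description.

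**Conclusion.** The control definition in the Randomization protocol section is wrong as written for this three-arm trial. It excludes one device under test and admits the other, and it conflicts with the abstract and the General description. The consequence is possible dilution of the control-versus-USD contrast (H0_1) and a mixed comparator for LS (H0_2), with unclear handling of such patients. This conclusion rests on the text alone.

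The size of the harm cannot be derived from the documents. On the assumptions stated, 20% USD use in controls would lower power by about 21 percentage points with the margin ignored (69% to 48%) or 22 with it subtracted (58% to 36%). Only this decline belongs to the point. The starting values below 80% come from the separate sample-size problem.

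**What to change.** Reconcile the Randomization protocol section with the abstract and the General description so that the control definition includes neither device under test. State that any use of LS or USD in a control patient is recorded as a conversion or deviation, using the item that the day-of-surgery data list already has for the control group. Which conventional devices control may use, for example bipolar coagulation, is for the investigators to settle, and all three descriptions should then say the same.

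The cost is a phrase in the protocol and the case report form, with some narrowing of what the Randomization protocol section now permits in controls. The sample size does not change. The correction is worth making before patients are operated on, because permitted USD use in controls cannot be undone in the analysis.

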##### Inclusion criteria

Allocation of donor liver via Eurotransplant (Leiden, The Netherlands) to recipientRecipients must be aged 18 years or olderA signed written informed consent for participation in the trial

##### Exclusion criteria

High urgency state of recipientPrevious LTCombined organ transplantInability to give informed consent

#### Sample size estimation

The total BL during piggyback LT usually ranges from 1000 to 2100 ml [22–24, 26]. Based on our own preliminary clinical experience on the use of the LS device for recipient hepatectomy, a reduction in BL during LT from 1500 ml to 835 ml with an SD of 560 ml can be expected. Because these results were obtained in an uncontrolled, retrospective study in which all procedures were performed by a single, very experienced surgeon, we have added a “buffer” of 200 ml in favor of a conservative yet robust sample size calculation. Therefore, a reduction in BL from 1500 ml to 1035 ml was chosen for this trial. This effect could be confirmed as statistically significant with a two-sided *t* test at a power of 80% and an alpha of 0.025 as well as a superiority margin of 50 ml with 23 patients in either group. Hence, at least 69 patients in total will be included in the intention-to-treat (ITT) analysis. Differences in the per-protocol and ITT analyses will be of certain interest with respect to the feasibility of the methods under investigation.

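### The only SD in the sample size calculation (560 ml) comes from a single-surgeon LigaSure series and was not buffered; even at that SD, 23 per arm gives about 58% or 69% power, not 80%, unless the 50 ml margin is added to the effect

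*Protocol article*

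**What the plan says.** *Sample size estimation* starts from the centre's preliminary experience: a fall from 1500 ml to 835 ml "with an SD of 560 ml can be expected". It says that this experience was retrospective and uncontrolled and came from one very experienced surgeon. For that reason it moves the expected device mean up by 200 ml, "in favor of a conservative yet robust sample size calculation", so that "a reduction in BL from 1500 ml to 1035 ml was chosen for this trial". It then states that 23 patients per group suffice for a two-sided t test "at a power of 80% and an alpha of 0.025", with a superiority margin of 50 ml. The abstract repeats the claim: "At 80% power and an alpha of 0.025 for both of the experimental groups".

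*Therapeutic effects* gives the origin of the SD: "BL during LT could be reduced to about 835 (± 560) ml using LS for recipient hepatectomy". The same section reports average losses of 1000 to 2100 ml at high-volume centres, without SDs. No SD for the control arm or the ultrasonic dissector (USD) arm appears anywhere in the article.

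**The concern.** There are two linked problems with the stated 80%.

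The first is where the SD comes from. An uncontrolled series of LS patients can supply an SD for LS patients. It cannot supply one for a control arm with an assumed mean of 1500 ml, or for the USD arm. The protocol accepts that a single-surgeon series may not carry over to the trial and corrects the mean for it. The same reason applies to the spread, which was left alone.

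The second is the stated power at that SD. The article names a 50 ml superiority margin but does not say how it enters the calculation. The null hypotheses in *Hypotheses* are written as plain equalities, and *Statistical design* does not mention the margin. Whether 23 per arm gives 80% power depends on this.

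At stake is the power claimed for a trial that describes itself as confirmatory. No treatment, test or patient number has to change.

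**Working it through.** **Inputs**
- Control mean 1500 ml, device mean 1035 ml, SD 560 ml, margin 50 ml, 23 per arm, 80% power, two-sided alpha 0.025: *Sample size estimation*.
- LS series 835 ± 560 ml: *Therapeutic effects*.
- Difference: 1500 − 1035 = 465 ml. Margin subtracted: 465 − 50 = 415 ml. Margin added: 465 + 50 = 515 ml.

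**Step 1: reproduce 23 per arm**

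Normal approximation: n per arm = 2 × (z for alpha + z for power)² × SD² / difference². With z = 2.241 for two-sided 0.025 and 0.842 for 80% power:
- 415 ml: 2 × (3.083)² × 560² / 415² = 34.6, so 35 (36 with the t distribution).
- 465 ml: 27.6, so 28 (29 with t).
- 515 ml: 22.5, so 23 (24 with t).

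At the stated alpha and sidedness, only the version that adds the margin gives 23. Two other routes also give 23 (24 with t), but each departs from the stated inputs: two-sided 0.05 (equivalently one-sided 0.025) with no margin, and one-sided 0.05 with the margin subtracted. All three use 560 ml in both arms. Since no other SD is given, that is why I say the figure was in effect applied to every arm.

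**Step 2: power at 23 per arm, SD 560 ml in both arms**

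Standard error = √((560² + 560²)/23) = 165.1 ml. Noncentrality = difference / standard error. Critical t = 2.321 on 44 degrees of freedom.

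| Handling of the margin | Difference | Noncentrality | Power |
|---|---|---|---|
| Subtracted | 415 ml | 2.51 | 58% |
| Ignored | 465 ml | 2.82 | 69% |
| Added | 515 ml | 3.12 | 78.5% |

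This table uses the protocol's own SD. The distance from 80% comes from the margin and alpha handling and owes nothing to where the SD came from.

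**Step 3: sensitivity to a larger control SD**

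The documents give no control SD, so every control value other than 560 ml below is an assumption. The values 700 and 800 ml are illustrative. The value 1006 ml applies the LS coefficient of variation to the control mean: 560/835 = 0.671, and 0.671 × 1500 = 1006. The device SD stays at 560 ml. Standard error = √((control SD² + 560²)/23), with Satterthwaite degrees of freedom.

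| Control SD (assumed) | Standard error | 415 ml | 465 ml | 515 ml |
|---|---|---|---|---|
| 560 ml | 165.1 ml | 58% | 69% | 78.5% |
| 700 ml | 186.9 ml | 47% | 57% | 67% |
| 800 ml | 203.6 ml | 39% | 49% | 58% |
| 1006 ml | 240.1 ml | 28% | 35% | 43% |

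**Step 4: what the buffer buys**

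The buffer cuts the assumed effect from 1500 − 835 = 665 ml to 465 ml, that is by 200/665 = 30%. If the true effect were 665 ml, with no margin, power at 23 per arm would be 95% at SD 560/560, 81% at 700/700 and 82% at 800/560.

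**The case against.** The best defence is that the source of the data is open to the reader: the article prints the LS mean and SD and names the single surgeon and the lack of controls. The buffer is also a real concession. Step 4 shows that if the true effect is near the preliminary one, 23 per arm still gives just over 80% with a noticeably larger SD. That stands. The calculation is conservative about the mean difference, and it would be wrong to say that the word has no basis at all. But the buffer protects against a larger SD only if the true effect exceeds the one the trial chose to power for. At the chosen effect nothing is held back for variance.

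It is also fair to object that no document shows a control SD above 560 ml. That stands too, so Step 3 is a sensitivity range and not an estimate.

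Several stronger readings are tempting and are not supported:
- A reader might infer that true power is 30% to 50%. That needs a control SD the documents do not give.
- A reader might infer that the SD's origin is what takes power below 80%. At SD 560 ml the shortfall comes from the margin and alpha handling.
- An SD at 67% of the mean might suggest strong skew. The documents describe no distribution.
- The plan to record each surgeon's experience suggests that operators will vary, which is reasonable to suppose, but the article does not say by how much.
- A reader might infer that a non-significant result will be presented as coming from an adequately powered trial. No section says how such a result would be read.

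**Conclusion.** The point holds on two counts.

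1. The only SD comes from an uncontrolled, single-surgeon LS series with mean 835 ml. It is in effect used for arms with assumed means of 1500 and 1035 ml, and it received no adjustment. The claim of conservatism is therefore supported for the mean difference and unsupported for the variance.
2. At that SD, 23 per arm and two-sided alpha 0.025, power is about 58% with the margin subtracted or 69% with it ignored. The stated 80% is approached, at 78.5%, only by adding the margin to the effect.

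The second count uses only the protocol's own figures and a common SD of 560 ml. The further loss from a larger control SD is conditional on the assumed values in Step 3. Restating the power is worthwhile because the trial relies on that figure and the correction is cheap.

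**What to change.** In *Sample size estimation*, with the power statement in the abstract brought into line, and keeping 23 per arm:

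1. State how the 50 ml margin enters the test (subtracted, ignored or added), and confirm the alpha and sidedness actually used. This has to come first, because every power figure depends on it.
2. Restate the power at SD 560 ml accordingly: about 58% at 415 ml or 69% at 465 ml under two-sided 0.025.
3. Say in that section that 560 ml is the SD of the single-surgeon LS series and that no SD was available for the control or USD arms, or cite one if the centre has it.
4. Add a sensitivity range for the control SD, labelled as an assumption. For example, control SD 700, 800 and 1006 ml with device SD 560 ml gives 47%, 39% and 28% at 415 ml, or 57%, 49% and 35% at 465 ml.
5. Limit the word conservative to the assumed mean difference.

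The cost is a few changed sentences and less favourable power figures. No patients are added, and the test and trial conduct stay as they are.

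### With the stated inputs, 23 patients per arm give about 69% power for the planned t test (58% if the 50 ml margin is tested), not 80%

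*Protocol article*

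**What the plan says.** All places are in the Protocol article.

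- **Sample size estimation, effect.** The starting point is that "a reduction in BL during LT from 1500 ml to 835 ml with an SD of 560 ml can be expected". A 200 ml buffer is then taken off the expected benefit: "Therefore, a reduction in BL from 1500 ml to 1035 ml was chosen for this trial".
- **Sample size estimation, test and result.** The reduction is to be shown by a two-sided t test. Its settings are "at a power of 80% and an alpha of 0.025". The margin and the resulting group size come last in that sentence: "as well as a superiority margin of 50 ml with 23 patients in either group".
- **Abstract, Methods/design.** The claim is repeated: "At 80% power and an alpha of 0.025 for both of the experimental groups, 23 subjects will be analyzed per protocol in each study arm".
- **Randomization protocol.** "Sixty-nine LT recipients are expected to be randomized into three groups of at least 23 patients each".
- **Hypotheses.** The formal nulls are equalities of blood loss between control and each device. The wording around them speaks of clinical relevance, but no 50 ml figure appears.
- **Statistical design.** Blood loss is compared by t tests with Bonferroni correction. No margin is mentioned.

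**The concern.** Every input needed to check the calculation is printed, and the result does not follow from them. A superiority margin makes a test harder to pass, so it should raise the sample size above that of a plain test. Yet 23 is too small even for the plain test at alpha 0.025.

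This is the only justification of size in a trial described as confirmatory, and it is presented as conservative because of the 200 ml buffer. If the true reduction with a device is 465 ml, the comparison of that device with control would miss it about 31% of the time (42% with the margin), not the 20% implied. A reader who trusts the 80% would take a non-significant result for a device as stronger evidence against the targeted effect than it is.

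**Working it through.** **Inputs** (Sample size estimation unless noted)

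- Difference: 1500 − 1035 = 465 ml.
- Difference net of the margin: 465 − 50 = 415 ml.
- SD: 560 ml, taken as common to all arms. This is an assumption: only one SD is given, and Therapeutic effects attaches ±560 ml to the centre's LigaSure series.
- Two-sided alpha: 0.025 per comparison (also in the Abstract).
- n = 23 per arm, so df = 2 × 23 − 2 = 44.

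**Step 1. Try to reproduce 23 (normal approximation)**

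n per arm = 2 × SD² × (z_alpha + z_power)² / difference², with z_power = 0.8416. At two-sided 0.025, z_alpha = 2.2414.

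- Margin subtracted: 2 × 560² × (2.2414 + 0.8416)² / 415² = 34.6, so 35.
- No margin: the same with 465² = 27.6, so 28.

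Neither gives 23.

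**Step 2. Sample size for the test the plan names (exact, noncentral t)**

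- No margin: 29 per arm, 3 × 29 = 87 in total.
- Margin subtracted: 36 per arm, 3 × 36 = 108 in total.

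**Step 3. Power at 23 per arm**

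Standard error of the difference = 560 × √(2/23) = 165.1 ml. The critical value of t with 44 df at two-sided 0.025 is 2.321. The noncentrality parameter is the difference divided by the standard error.

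| Test | Difference | Noncentrality | Power (exact t) | Power (normal) |
|---|---|---|---|---|
| Against zero | 465 ml | 2.816 | 68.9% | 71.7% |
| Against the 50 ml margin | 415 ml | 2.513 | 57.9% | 60.7% |

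The choice between exact and approximate methods does not close the gap to 80%.

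**Step 4. What 23 per arm can detect with 80% power**

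- Against zero: a true reduction of about 524 ml.
- Against the margin: 524 + 50 = 574 ml.
- Alternatively, with the reduction held at 465 ml, the SD would have to be no more than about 496 ml (no margin) or 443 ml (with margin).

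**Step 5. Which altered inputs return 23**

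| Change to the stated inputs | n (normal) | Exact-t power at 23 |
|---|---|---|
| Two-sided 0.05 (or one-sided 0.025), margin dropped | 22.8, so 23 | 78.6% |
| Two-sided 0.025, margin added: 465 + 50 = 515 ml | 22.5, so 23 | 78.5% |
| One-sided 0.05, margin subtracted | 22.5, so 23 | 79.7% |

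Each contradicts at least one stated input, and each needs 24 per arm by the exact t calculation.

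**The case against.** **The margin may not belong to the test.** Hypotheses and Statistical design describe plain equality tests, so a reader might infer too much by taking 58% as the power under the plan's own rule. This stands. The planned analysis has 69% power, and 58% applies only if the margin mentioned under Sample size estimation is tested. Neither figure is 80%.

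**The slip is identifiable.** A reader might infer that the margin was added to the effect instead of subtracted. The document shows no such calculation, and other changes return 23 equally well. The origin cannot be determined.

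**The trial as a whole is less weak than one comparison.** If both devices truly reduce blood loss by 465 ml, the chance that at least one comparison is significant is about 83 to 84% (simulation with a shared control arm and no margin). That limits what may be said about a trial negative on both devices. It does not rescue the 80%, because the text applies the alpha and the 23 patients to each comparison with control: "At 80% power and an alpha of 0.025 for both of the experimental groups".

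**The numbers are minima.** Both 23 per group and 69 in total are stated as lower bounds, so the final size is not capped. The error lies in the power claimed at that minimum.

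**An article condenses the protocol.** This would excuse a missing detail. Here the inputs and the result are both printed and disagree, which a separate analysis plan cannot mend.

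**Conclusion.** The 80% power claim is wrong under either reading of the margin. At 23 per arm, power per comparison is about 69% for the planned equality t test, a shortfall of about 11 percentage points. It is about 58% if the 50 ml margin is tested, a shortfall of about 22 points. Holding 80% would take 29 or 36 per arm.

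These figures assume a common SD of 560 ml, two-sided alpha 0.025 for each comparison and a true reduction of 465 ml. They do not show how 23 was obtained, nor that the trial must be enlarged. They show that the stated power cannot stand beside the stated inputs. Because this is the sole size justification of a confirmatory trial, the statement must be corrected.

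**What to change.** Keep 69 patients and replace the power statement in Sample size estimation, with the matching sentence in the Abstract, by wording such as:

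> With 23 patients per arm, two-sided alpha 0.025 and a common SD of 560 ml, power per comparison is 69% for a 465 ml reduction tested against zero (58% against a 50 ml margin); 80% power corresponds to a true reduction of about 524 ml (574 ml with the margin).

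Also make Hypotheses, Sample size estimation and Statistical design agree on whether the 50 ml margin is part of the primary test, and keep only the figures that match that choice.

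Cost: wording only, with no extra patients and no change in conduct. The downside is a less favourable stated power. A sponsor who wishes to keep the 80% claim at 465 ml would need 87 patients in total without the margin, or 108 with it, before any allowance for losses.
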